### Multifactorial movement analysis

Patients perform four tasks:

(1.) upright standing;

(2.) starting to walk;

(3.) linear free gait (with and without a cognitive task);

(4.) gait along a curvilinear trajectory.

Tests are carried out in the order listed above as already described with minor modifications [35], if possible given the clinical status of the patient, before and after MSC therapy. Each test requires 4–8 walks, at intervals of about 5–10 minutes, on a platform about 10 meters long at a comfortable speed. The cognitive task consists in a calculation (counting backwards, starting from 100 and subtracting 7 at a time). The patients are not corrected or stopped if they make mistakes in calculating. The curvilinear test consists in straight walking for 2 meters towards the center of the platform and then a curvilinear trajectory with an angle of 90° for another 2 meters. Data are collected with a SMART optoelectronic movement analysis system (BTS SpA, Italy) equipped with: (i) optoelectronic system (six cameras with 60 Hz acquisition frequency) to establish the position of 29 reflecting markers applied onto the skin of the patients at anatomical landmarks (ii) three dynamometric platforms (KISLER, GmbH, Winthertur, Switzerland) with 960 Hz acquisition frequency to record ground reaction forces; (iii) TELEMG telemetric electromyograph (BTS SpA) and a FreeEMG wireless electromyography to measure muscular activity of tibialis anterior and soleus bilaterally.

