#### Multifactorial movement analysis

The data related to each of the four tests will be normalized and the mean of the values related to each variable recorded during the 8 walks will be calculated. The data before and after MSC therapy will be compared using Wilcoxon’s signed rank test for matched pairs, considering the patients before and after treatment as a pair (the results at each follow-up visit will be assessed separately). Moreover, the results obtained in PSP patients will be compared with those obtained in the group of age-matched healthy volunteers using the non-parametric Mann–Whitney U Test.

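### Dual-task gait is described with a single calculation (100 minus 7s) and no alternate form, so a practice gain, if there is one, would not be separated from an MSC effect in the planned before-after test

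*Protocol article*

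**What the plan says.** All references are to the Protocol article.

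- **Task.** Under Multifactorial movement analysis (Methods), the third of four movement tasks is "linear free gait (with and without a cognitive task"). The load is then defined: "The cognitive task consists in a calculation (counting backwards, starting from 100 and subtracting 7 at a time"). No second start number, second subtrahend or familiarisation run is mentioned.
- **Repetition within a session.** "Each test requires 4–8 walks, at intervals of about 5–10 minutes".
- **Repetition across sessions.** The tests are done "if possible given the clinical status of the patient, before and after MSC therapy".
- **Errors.** "The patients are not corrected or stopped if they make mistakes in calculating".
- **Analysis.** In the section of the same name under Statistics: "The data before and after MSC therapy will be compared using Wilcoxon’s signed rank test for matched pairs", and "the results at each follow-up visit will be assessed separately". The only between-group gait comparison there is of PSP patients with healthy volunteers.
- **General considerations (Statistics).** Within-subject tests of each variable are planned before versus after MSC and before versus after sham. The MSC test uses 20 pairs, 10 from each sequence. No test of change after MSC against change after sham is stated.

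**The concern.** A dual-task condition is informative only while the second task keeps demanding attention. If the same short series is recited repeatedly, it may become familiar and compete less with walking. Dual-task gait could then improve, or decline less, with no change in the disease.

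A before-after comparison within patients has no means of removing such a gain, because the later measurement always comes with more exposure than the earlier one. The secondary objective counts stabilisation as well as improvement of motor function, so a practice gain that merely masked decline could also be read as a favourable result.

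**Working it through.** **1. No planned figure to reproduce.** The article gives no power, effect size or practice effect for gait. The one related count adds up: 10 + 10 = 20 pairs.

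**2. Length of the series.** 100, 93, 86, ... 2. Since 100 − 14 × 7 = 2, there are at most 14 subtractions.

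**3. How much of it one walk uses.** The platform is about 10 m long. Assume, since the article does not say, a speed of 0.5 to 1.0 m/s and 2 to 5 s per subtraction. A walk then lasts 10/1.0 = 10 s to 10/0.5 = 20 s and holds 10/5 = 2 to 20/2 = 10 subtractions. If each walk restarts at 100, these are always the opening ones.

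**4. Number of exposures.** The article gives 4–8 walks per test. It does not say whether walks with and without the cognitive task share that number, nor how many gait sessions there are, so both are varied here.

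| Sessions (assumed) | All 4–8 walks are dual-task | Half are dual-task (2–4) |
|---|---|---|
| 2 | 8–16 | 4–8 |
| 4 | 16–32 | 8–16 |

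**5. What the planned test would do with a shift.** Simulation of the signed-rank test: 20 pairs, normally distributed changes with SD 1, two-sided 0.05 (the article does not state sidedness), no MSC effect, 10,000 runs. The shift is the assumed net movement from practice, in SDs of the paired change. The last column is a Mann–Whitney test of change between two arms of 10 with the same shift in both.

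| Assumed net shift (SD) | Before-after test significant in the benefit direction | Between-arm test significant (two-sided) |
|---|---|---|
| 0 | 2.3% | 4.4% |
| 0.1 | 6.3% | 4.6% |
| 0.2 | 12.6% | 4.2% |
| 0.3 | 23.7% | 4.0% |
| 0.5 | 54.4% | 4.2% |
| 0.8 | 91.1% | 4.2% |

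The table shows how the two analyses respond to a given shift. It is no evidence that a shift of any particular size occurs. Decline from the disease would reduce the net shift, possibly to zero or below.

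**The case against.** The strongest case against the point has five parts.

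- **The restart is not stated.** A reader might infer that the article prescribes the same sum from 100 on every walk and at every visit. It does not say so. It describes the task once and refers to a previously published procedure with minor modifications. A restart at 100 is the natural reading, and no other version is given, but the full protocol may vary the start number. That would close the point.
- **Learning is not shown.** A reader might go further and infer that patients do learn the series and that practice will pass for an MSC benefit. The article reports no practice effect. Uncorrected mistakes make it harder to learn the right answers, although they do not rule out familiarity with the task. Excluding patients with MMSE below 24 makes some learning plausible, but does not show that numbers are retained over months. PSP is progressive and involves the prefrontal cortex, which works against a gain. The net direction is therefore open.
- **Unequal exposure between the sequences is not documented.** It is tempting to say that delayed-treatment patients arrive at their pre-MSC test already practised, while immediate-treatment patients do not. That depends on gait testing at entry in the delayed arm, which the readable text does not settle. Earlier exposure could also shrink the later practice gain in that arm.
- **Sham periods exist.** If gait is among the variables tested before and after sham, practice without MSC would become visible. This stands, but a within-patient sham test does not subtract practice from the MSC result. The lack of a stated MSC-versus-sham comparison is the broader weakness.
- **A constant task is ordinary standardisation.** Varying start numbers adds some noise to a small sample. This stands as a cost of the change.

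**Conclusion.** The point holds in a limited form. The article names one calculation and no alternate form for a repeated test, and the stated gait analysis is a before-after comparison that could not separate a practice gain from an MSC effect in the dual-task condition.

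This rests on the natural reading that the calculation starts at 100 each time. The amount of bias cannot be derived from the article. The rates above depend wholly on assumed shifts, with no decline and no MSC effect.

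The reach is narrow: one condition of one of four movement tasks, under a secondary objective of a phase I safety trial. Single-task gait, the clinical scales, imaging and the primary safety objective are unaffected. It is an optional refinement to consider.

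**What to change.** 1. **Patients not yet tested.** In Multifactorial movement analysis (Methods), replace the single start at 100 with a pre-set list of start numbers of similar difficulty, varied by walk and visit and the same for all patients. Give one familiarisation run at entry in both arms.
2. **Patients already tested.** Keep the start at 100 throughout, so that their before-after pairs stay comparable. Switching them midway would introduce a bias of its own.
3. **Record** the number of correct subtractions per walk. This would help show whether practice occurred.
4. **Analysis.** In the corresponding Statistics section, state that dual-task change after MSC is read against dual-task change after sham. The randomised first 6 months give the cleanest comparison, because equal practice in both arms cancels.

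If the full protocol already varies the start number, a sentence saying so is enough.

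**Cost.** About a page listing start numbers and a line in the gait manual. The downside is slight variation in difficulty between start numbers. With a common list, any difference in difficulty between visits would shift all patients alike. It would remain in a before-after comparison but cancel between arms tested at the same visits.

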### Neuropsychological assessment

The following tests are performed:

–Mini Mental State Examination (MMSE) [36]

–Neuropsychological measures: verbal comprehension; perceptual organization, immediate memory (story, design, word list learning), delayed memory (story, design, word list recall), word list recognition, language (confrontation naming, category fluency, letter fluency, auditory comprehension), attention/concentration, visuospatial ability (block design), processing speed, executive functioning (cognitive flexibility).

### Quality of life

Quality of life is assessed by asking the patients to fill-in the PDQ-8 questionnaire [37] at baseline, and 6 and 12 months after MSC therapy.

### Neuroimaging

All patients perform a longitudinal neuroimaging assessment at baseline and 6, 12 and 18 months after MSC therapy, using striatal dopamine transporter Single Photon Emission Computed Tomography (SPECT) and Positron Emission Tomography (PET) using a tropanic tracer labeled with Iodine-123 (FP-CIT) for SPECT imaging and Iodine-124 (Beta-CIT) for PET/TC imaging. SPECT studies are carried after intravenous administration of 110-140 MBq of ^123^I-FP-CIT (Datscan®, GE-Health, Amersham, UK) performed 30–40 minutes after thyroid blockade (10–15 mg of Lugol solution per os) in all subjects. ^18^ F-fluorodeoxyglucose positron emission tomography (FDG-PET/TC) is performed 4–6 hours and 20–24 hours after intravenous injection of 18–30 MBq of ^124^I- Beta-CIT. All patients undergo ^18^ F-fluoro-2-deoxy-D-glucose positron emission tomography scanning (FDG-PET) at rest, after intravenous injection of 285 to 296 MBq.

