	-Women of child-bearing age;
	-Participation in another clinical trial with experimental treatment in the last 30 days;
	-Brain MRI evidence of severe vascular abnormalities, space-occupying lesions or normal pressure hydrocephalus.

The first 5 patients are treated in an open phase with autologous MSC therapy with the same procedures as for the randomized phase.

After these first 5 patients have been followed-up for a minimum of 2 months from the cellular infusion, the ISS Data Safety Monitoring Board will review the safety data prior to open the accrual of the subsequent randomized controlled phase.

In the randomized phase the patients undergo to:

–immediate autologous MSC therapy followed by delayed sham or

–immediate sham followed by delayed autologous MSC therapy.

The delay amounts to 6 months and all patients will be followed-up for at least 12 months after MSC therapy, so the total duration of the study is 18 months. The study design is shown in Figure 2.

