### Statistics

#### General considerations

As noted above, the safety of cellular therapy administration in the first five patients will be reviewed by the Data Safety Monitoring Board. These reviews will be shared with our institutional IRB. If the treatment appears safe, as determined by the Data Safety Monitoring Board with institutional IRB agreement, the protocol may be reopened to treat a total of 20 patients.

For statistical analysis of efficacy endpoints, descriptive statistics are computed for variables of interest (mean and SD for continuous variables and frequencies for categorical variables). Test results are summarized over time using appropriate graphical or tabular formats. The non parametric pair wise Wilcoxon rank sum test will be used to investigate each variable within subject and between the same subject at different follow-up (e.g. pre- vs. post-MSC, pre- vs. post-sham, etc.). The use of a non-parametric test has been considered the most appropriate since the distribution of the variable is not known and the number of observations is relatively small. For each time point, the test will be performed with 20 paired values (the values before and after MSC therapy in the 10 subjects allocated to immediate treatment plus the 10 subjects allocated to the delayed treatment).

P-values < 0,05 will be considered statistically significant. Additional summary statistics are also considered as appropriate to the data.

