In this study a “pure” control group treated with placebo solution administered by the same route in a double-blinded manner is missing since this option was considered not acceptable by the ethical point of view by the investigators, given the potential harm of a cerebral artery catheterization procedure that is not justified by a potential benefit. Nevertheless, the patients enrolled in the control harm receive a simulated arterial catheterization and administration procedure and the neurologist and the neuro-radiologist who perform the follow-up evaluation are blinded. In this way, we exclude the placebo effect with the best precision.

In conclusions, the presented protocol is the first attempt to understand if MSC can be safely administered and can exert a beneficial effect in PSP patients. We believe that the results of this trial will help to improve the knowledge around the neuroprotective properties of MSC that might be exploited in other several neurodegenerative disorders.

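### Imaging timed from MSC therapy puts the delayed arm's last scan at month 24 of an 18-month study, and the imaging and PDQ-8 times as written give that arm no change over its MSC-free sham period

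*Protocol article*

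**What the plan says.** All references are to the protocol article.

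- **Neuroimaging:** "All patients perform a longitudinal neuroimaging assessment at baseline and 6, 12 and 18 months after MSC therapy". The anchor is MSC therapy, and the sentence covers every patient.
- **Quality of life:** PDQ-8 is completed "at baseline, and 6 and 12 months after MSC therapy", with the same anchor and no 18-month visit.
- **Study design:** one randomised arm receives MSC first and sham later. The other receives "immediate sham followed by delayed autologous MSC therapy". On timing, the section says: "The delay amounts to 6 months and all patients will be followed-up for at least 12 months after MSC therapy". From this it draws the overall length: "so the total duration of the study is 18 months".
- **Statistics, General considerations:** each variable is to be tested within subject, "e.g. pre- vs. post-MSC, pre- vs. post-sham, etc". On numbers: "For each time point, the test will be performed with 20 paired values", made up of 10 immediate-arm and 10 delayed-arm patients.
- **Statistics, Neuroimaging assessment:** imaging is analysed by ANOVA in SPM at p<0.01.
- **Discussion:** "the neurologist and the neuro-radiologist who perform the follow-up evaluation are blinded", and the simulated procedure is offered as the means of excluding a placebo effect.

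**The concern.** The two arms receive MSC six months apart, so a visit schedule anchored on MSC runs on two different study calendars. This has three consequences.

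First, the longest imaging interval does not fit inside the study for the delayed arm.

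Second, the delayed arm's first six months are the only sham period in the trial that no MSC has preceded. A change over those months needs a measurement at each end, and the written times supply one.

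Third, if the arms are scanned at different times since entry, scan timing could reveal allocation to a reader who knows the time since entry.

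Imaging is named in the secondary objective, and the Discussion says the sham control was included so that efficacy could be documented. The Discussion also faults earlier studies for a lack of objective measurement. Under the written schedule, imaging and PDQ-8 would lose the comparison the sham arm exists to provide. A month-6 scan that is not done cannot be recovered later.

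**Working it through.** **Inputs.** Delay to MSC in the delayed arm: 6 months (Study design). Minimum follow-up after MSC: 12 months (Study design). Imaging: baseline and MSC + 6, 12, 18 months (Neuroimaging). PDQ-8: baseline and MSC + 6, 12 months (Quality of life). Patients: 10 per arm (General considerations).

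**Step 1: the plan's own figure.** Study length = delay + follow-up after MSC = 6 + 12 = 18 months. This reproduces the stated duration, so month 0 is the first procedure and month 18 is the end.

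**Step 2: visits in study time.** Study month = month of MSC (0 immediate, 6 delayed) + stated months after MSC. The text does not say whether baseline means study entry or just before MSC, so both are shown.

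| Arm and reading of baseline | Imaging, study month | PDQ-8, study month | Measurements in months 0–6 |
|---|---|---|---|
| Immediate (readings coincide) | 0, 6, 12, 18 | 0, 6, 12 | 0 and 6 |
| Delayed, baseline at entry | 0, 12, 18, **24** | 0, 12, 18 | 0 only |
| Delayed, baseline just before MSC | 6, 12, 18, **24** | 6, 12, 18 | 6 only |

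**Step 3: overrun.** Last delayed-arm scan: 6 + 18 = 24, and 24 − 18 = 6 months past the end, on both readings. The last delayed-arm PDQ-8 is at 6 + 12 = month 18, which fits. The overrun therefore concerns imaging only.

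**Step 4: patients at 18 months after MSC.** Immediate arm 10, delayed arm 0, total 10 of 20.

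**Step 5: the sham period.** A change over months 0 to 6 needs values at both months. The immediate arm has both, under MSC. The delayed arm has one on either reading, so 0 of its 10 patients can supply a sham-period change in imaging or PDQ-8 as the text stands. With baseline at entry, the delayed arm's value before MSC is also six months old when MSC is given, so its before/after-MSC change includes the sham period.

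**Step 6: the other sham period.** The immediate arm receives sham at month 6 and has imaging and PDQ-8 at months 6 and 12. A pre/post-sham change exists there, but it follows MSC and cannot be separated from any continuing MSC effect.

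**Step 7: calendars.** With baseline at entry, only the immediate arm is scanned at month 6. With baseline just before MSC, both arms are scanned at month 6, and month 0 is where they differ.

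**The case against.** The strongest reply is that this is a wording slip in a condensed article. The 6, 12 and 18-month pattern fits an 18-month study exactly if counted from the first procedure. The planned pre- versus post-sham tests show that measurements around the sham were intended. The study-design figure is not shown and may carry a month-6 visit. Baseline may also be meant to repeat before each procedure, in which case the delayed arm would have months 0 and 6 and the sham-period gap would close. All this is fair, and it limits how firmly the gap can be asserted. However, none of it is written in the Neuroimaging or Quality of life sections, and a repeated baseline would not move the month-24 scan. Nor does the wording that follow-up lasts at least 12 months, because the same sentence puts the total at 18.

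Four stronger inferences are tempting, and the documents do not support them:

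- **No sham change exists at all.** It does in the immediate arm, months 6 to 12, though after MSC.
- **The schedule unblinds the readers.** That depends on the reading of baseline and on readers knowing time since entry. The article says evaluators are blinded and does not say whether they see scan dates.
- **The drop from 20 to 10 patients implies a particular loss of power for the paired rank test.** Imaging is assigned to ANOVA in SPM at p<0.01, and PDQ-8 has no 18-month visit. A rank-test figure fits neither.
- **The trial's main aim is compromised.** The primary objective is safety; imaging belongs to the secondary objective, and PDQ-8 is not primary either.

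**Conclusion.** The point holds in two parts of different strength.

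**Firm:** the imaging schedule and the stated duration contradict each other for the delayed arm, by six months. At 18 months after MSC at most 10 of the 20 patients can contribute. This needs no assumption beyond the six-month delay and the 18-month total, both stated.

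**Conditional on the text as written:** the delayed arm has one of the two measurements needed for a change over months 0 to 6, for both imaging and PDQ-8. No sham change free of earlier MSC, and no randomised MSC-versus-sham comparison over those months, can then be formed for these outcomes. This would be withdrawn if the full protocol or the missing figure schedules measurements at both month 0 and month 6 in that arm.

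Disclosure of allocation through scan timing is a possible further consequence, subject to the conditions above. The point is confined to imaging and PDQ-8. It should be settled before delayed-arm patients reach month 6.

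**What to change.** Reconcile Study design, Quality of life, Neuroimaging and General considerations as follows:

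1. Count imaging and PDQ-8 visits from the first procedure in both arms: months 0, 6 (before the second procedure), 12 and 18.
2. Delete the scan at 18 months after MSC for the delayed arm.
3. Name month 6 as the controlled MSC-versus-sham comparison for these outcomes.
4. State that follow-up beyond 12 months after MSC exists only in the immediate arm, and limit the claim of 20 paired values to time points where both arms contribute.

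**Cost.** An amendment to the visit schedule. Imaging stays at four sets per patient: the immediate arm is unchanged, and the delayed arm's month-24 set is replaced by month 6 (if baseline is entry) or month 0 (if baseline is just before MSC). PDQ-8 goes from three to four questionnaires per patient: month 18 is added in the immediate arm, and month 6 or month 0 in the delayed arm. What is given up is a delayed-arm scan 18 months after MSC, which the stated study length already excludes. A common calendar also removes scan timing as a clue to allocation.

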### Safety

Toxicity is evaluated following the National Cancer Institute Common Toxicity Criteria Manual (CTCAE v 4.0) [38]. At screening demographic information, medical history and specific history of PSP (age at onset, signs and symptoms, previous investigations, with particular reference to neuroimages, treatment) are collected. Patients are monitored closely after the MSC/sham procedure for 3 hours at the day-hospital of the Diagnostic and Interventional Neuroradiology Unit and subsequently at the ward of the Neurosurgery Unit until discharge the next day. A general medical examination and routine laboratory tests are performed at every visit, plus any further investigations that are deemed necessary according to the findings of the general medical examination.

